### Psychological Examinations

The cognitive function and mental status of the subjects will be evaluated in each institute by well-trained neurologists or psychologists who are familiar with CDR (at baseline and 2 years), MoCA (at baseline, 1 and 2 years), and geriatric depression scale (at baseline).

### Clinical Frailty Scale

The frailty at baseline and 2 years (32) will be assessed in each institute by well-trained neurologists using the Clinical Frailty Scale version 2.0 (24).

### Data Management

An electronic data capture system, Research Electronic Data Capture (REDCap; Vanderbilt University, Nashville, TN, USA) (33), will be used for the collection and management of all data. Brain MRI data will be sent to the Central Evaluation Committee, and the data will be assessed by three neurologists belonging to the committee. Dental findings will be evaluated and stored by dentists in the Department of Pediatric Dentistry at Osaka University. All data will be collected and integrated at the NCVC. The data managers will perform quality control at each step of data handling to ensure the reliability of all data related to the study.

### Statistical Analyses

For the primary outcome, the incidence of newly developed CMBs will be compared between patients with and without Cnm-positive *S. mutans* using a quasi-Poisson regression model, adjusted for age, sex, risk factors, antithrombotic medication, history of heart disease, history of cerebrovascular diseases, and dental findings. For the secondary outcomes, which include the incidence of symptomatic ICH or IS, all-cause mortality, and total hemorrhagic events, the survival time curves will be derived for each group using the Kaplan-Meier method and the survival rates will be compared between the two groups using the log-rank test and Cox proportional hazard models. The changes of scores based on frailty scale scoring, the cognitive tests from baseline to 2 years, and the antibody titers against periodontal pathogens at baseline will be compared between patients with and without Cnm-positive *S. mutans* using generalized linear mixed models for repeated measurements based on data distributions. Statistical analysis will be conducted using SAS version 9.4 (SAS Institute, Cary, USA).

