## Methods

### Study Design and Setting

The RAMESSES study is a multicenter longitudinal prospective cohort study. The purpose of the study is to investigate the relationship between Cnm-positive *S. mutans* and SVD. The study will involve 15 institutes, including the National Cerebral and Cardiovascular Center (NCVC) as the central coordinating center located in Japan. The study will register 230 patients who develop stroke within 1 year after onset and are diagnosed with at least one hemorrhagic lesion involving CMBs or ICH in the deep area detected on T2^*^WI. The primary and secondary outcomes will be assessed at baseline, 6, 12, 18, and 24 months after written informed consent is obtained. We will conduct the assessments according to Table 1 for 2 years. The study protocol has been approved by the Research Ethics Committee of each participating center (NCVC protocol number: M29-133), and this study has been registered with the University Hospital Medical Information Network (UMIN) Clinical Trials Registry (UMIN-CTR: UMIN000045559). Each participant will be provided a detailed explanation of the purpose and potential risks of the study, and written informed consent will be obtained.

**Table 1 T1:** Study schedule.

	**Baseline**	**Follow-up visits**			
		**6 months**	**1 year**	**1.5 years**	**2 years**
Patient characteristics	X				
Physical examinations	X	X	X	X	X
Brain MRI	X		X		X
MoCA	X		X		X
CDR	X				X
GDS	X				
Clinical Frailty Scale	X				X
Laboratory tests	X				
Dental examinations	X				
Assessment of *cnm*	X				
Serum antibody titers against periodontal pathogens	X				

*MRI, magnetic resonance imaging; MoCA, Montreal Cognitive Assessment; CDR, Clinical Dementia Rating; GDS, Geriatric Depression Scale. The mark ‘X' means conduction of assessments*.

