### MRI Evaluation

All 3.0 Tesla MRI examinations will be performed using the following standardized MR imaging protocol. All slices will be taken parallel to the orbitomeatal line from the base of the skull to the vault. The imaging protocol includes T2^*^WI, fluid-attenuated inversion recovery (FLAIR), diffusion-weighted imaging (DWI), and apparent diffusion coefficient. The sequence parameters of T2^*^WI are as follows: voxel size, 0.7 × 0.7 × 4.0 mm; slice gap, 0 mm; flip angle, 20°; field of view, 230 mm; echo time, 12 ms; repetition time, 686 ms. The sequence parameters of FLAIR are as follows: voxel size, 0.7 × 0.7 × 5.0 mm; slice gap, 1 mm; flip angle, 150°; field of view, 230 mm; echo time, 114–117 ms; repetition time, 12,000 ms. The sequence parameters of DWI are not restricted. CMBs and symptomatic ICH will be evaluated using T2^*^WI-MRI. CMBs in deep or lobar areas indicated below will be defined and counted according to the Brain Observer MicroBleed Scale (5) or the Microbleed Anatomical Rating Scale (22). CMBs will be categorized into three groups: (1) deep CMBs defined elsewhere (5, 22), (2) lobar CMBs in the cortical gray or subcortical white matter, and (3) subtentorial CMBs in the cerebellum or brain stem. CMBs in any brain region (any CMB) will also be recorded. Newly developed CMBs will be recorded at follow-up after 1 and 2 years. Symptomatic ischemic stroke (IS) will be evaluated by DWI. Lacunes and WMHs will be evaluated using FLAIR images. A lacune is defined as a supratentorial hypointense lesion 3–15 mm in diameter with a hyperintense rim. Periventricular hyperintensities (PVHs) and deep white matter hyperintensities (DWMHs) will be scored using the Fazekas scale (23).

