### Dental Examination and the Evaluation of Cnm-Positive *S. mutans*

Dental examinations will be conducted by well-trained dentists at each institute. Dental examinations will include (1) checking for the presence of dental caries; (2) dental radiography; (3) probing pocket depth assessed from the free gingival margin to the bottom of the sulcus or pocket; (4) full-mouth bleeding score, which is defined as the number of sites with gingival bleeding on probing divided by the total number of sites per mouth and multiplied by 100 (28); (5) the number of remaining and deficit teeth excluding the third molars; (6) the decayed, missing, and filled teeth (DMFT) index as an indicator of dental history or health (29). Sample collection and detection of Cnm-positive *S. mutans* will be performed using the following standardized protocol: oral saliva and dental plaque specimens will be collected from the patients using Seed-swab Type ⋎3 (Eiken Chemical, Tokyo, Japan). These samples will be inoculated on Mitis-Salivarius medium with bacitracin (MSB, 100 U/ml; Sigma-Aldrich, St. Louis, MO, USA) and 15% sucrose (MSB agar) and anaerobically incubated at 37°C for 48 h. The *S. mutans* colonies will be isolated and cultured in Brain Heart Infusion Broth (Difco Laboratories, Detroit, MI, USA) at 37°C for 24 h. Then, DNA from each strain will be extracted and analyzed by polymerase chain reaction using species-specific MKD primers to identify *S. mutans* isolates (27) and *cnm* primers to detect the *cnm* gene (16). A collagen-binding assay with type I collagen will be conducted to examine the collagen-binding activity of each isolated *S. mutans* strain, according to the method described elsewhere (30), with some modifications (27). The activity tests will be performed under fixed conditions using 1 mg of type I collagen and 1 × 10^10^ bacterial cells. The activity for each strain is expressed as a percentage compared with the positive control *S. mutans* TW871, which has 100% binding activity to type I collagen (27). These experiments will be conducted by a researcher who is blinded to the clinical information.

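### The primary model's stated covariate list leaves out institute, although this is a non-randomised comparison across 15 institutes

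*Protocol article*

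**What the plan says.** All references are to the protocol article.

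**Model.** Under Statistical Analyses, the number of new microbleeds is compared between Cnm-positive and Cnm-negative patients "using a quasi-Poisson regression model", "adjusted for age, sex, risk factors, antithrombotic medication, history of heart disease, history of cerebrovascular diseases, and dental findings". Institute is not named as a covariate, stratum, random effect or cluster. Study Design and Setting states: "The study will involve 15 institutes, including the National Cerebral and Cardiovascular Center (NCVC) as the central coordinating center located in Japan".

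**What is standardised.** MRI Evaluation states: "All 3.0 Tesla MRI examinations will be performed using the following standardized MR imaging protocol". It then sets the T2* parameters. Under Data Management, "Brain MRI data will be sent to the Central Evaluation Committee, and the data will be assessed by three neurologists belonging to the committee". The section on dental examination and Cnm prescribes one procedure for collecting and testing oral samples, with laboratory work done blind to clinical information.

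**What is local.** The same section states: "Dental examinations will be conducted by well-trained dentists at each institute". Data Management adds: "Dental findings will be evaluated and stored by dentists in the Department of Pediatric Dentistry at Osaka University". The sections on psychological examinations and the Clinical Frailty Scale place the rating of MoCA, CDR and frailty in each institute.

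**The concern.** In a cohort, institute can confound. Hospitals may differ in the patients they enrol and in how well blood pressure and other risk factors are controlled, and both affect the rate of new microbleeds. If institutes also differ in the share of Cnm carriers among their patients, and the two differences run together, the model credits part of a hospital difference to Cnm.

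Dental findings add a second route. They are an adjustment covariate, and measures such as probing depth and bleeding on probing are taken in the mouth by the local examiner. Central evaluation of the recorded findings cannot re-measure them. Differences between examiners therefore enter the covariate and make its adjustment less reliable across sites.

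The study aims to establish the role of Cnm-positive *S. mutans*. A reader will ask whether the association holds within institutes, and the stated model does not answer that.

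**Working it through.** The plan gives no figure for between-site variation, so there is none to reproduce on this point. The one related figure is the number of carriers, and it agrees with its inputs: 0.12 × 223 = 26.8, or 27.

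**Inputs from the article:** 15 institutes; 223 patients needed, of whom 27 are Cnm-positive; planning IRR 4.3; Cnm prevalence of 7–20% across earlier studies.

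**Assumptions (not in the article):** the 7–20% range is borrowed as a range between sites; half the patients come from each of two kinds of site; the rate of new microbleeds is r times higher at the high-prevalence sites; the true IRR is 1; no covariates are adjusted for.

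**Step 1. Where each group comes from.**
- Carriers from high-prevalence sites: 0.20 / (0.20 + 0.07) = 0.741
- Non-carriers from high-prevalence sites: 0.80 / (0.80 + 0.93) = 0.462

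**Step 2. Apparent IRR when Cnm has no effect.**

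Crude IRR = (0.259 + 0.741 r) / (0.538 + 0.462 r)

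| Site prevalences | r = 1.5 | r = 2 | r = 3 |
|---|---|---|---|
| 7% vs 20% | 1.11 | 1.19 | 1.29 |
| 9% vs 15% | 1.06 | 1.10 | 1.15 |
| 12% vs 12% | 1.00 | 1.00 | 1.00 |

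The second row uses the same formula with 0.15/0.24 = 0.625 and 0.85/1.76 = 0.483. The bias can also run the other way. If the 20% sites have the lower rate (r = 1/1.5 or 1/2), the first-row formula gives 0.89 or 0.82.

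**Step 3. Upper limits for 7% vs 20%.** As r grows without bound, the equal-halves case tends to 0.741/0.462 = 1.60. For any mix of the two kinds of site, the limit is the prevalence odds ratio: (0.20/0.80) / (0.07/0.93) = 3.3. Both are below 4.3.

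**Step 4. Effect on the test.** A simulation used 15 sites, 230 patients, 12% carriers, a true IRR of 1, an assumed mean of 0.2 new microbleeds per patient with overdispersion, a between-site SD of 0.5–0.7 on the log rate and of 0.4 on the logit prevalence. It ran 500 times per setting (Monte Carlo error about 1 percentage point). The nominal level is 5%.

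| Correlation of site rate and site prevalence | Type I error, no institute term |
|---|---|
| 0 | 3–5% |
| 0.5 | 6–7% |
| 1 | 8–10% |

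With site fixed effects it was 4–6% throughout. A random intercept was not simulated.

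**Step 5. Sparseness.** 27/15 = 1.8 carriers per institute on average. An institute with 15 patients at 12% prevalence has no carrier with probability 0.88^15 = 0.147. With equal-sized sites, about 15 × 0.147 = 2.2 institutes would have none and would tell us nothing about Cnm within the institute.

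**The case against.** The strongest case on the other side has four parts.

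- **Detection is standardised.** A reader might infer that site differences in finding microbleeds or Cnm pass straight into the comparison. The article does not support that. Field strength and T2* parameters are set, one committee reads the scans, and collection and testing of oral samples follow one procedure with blinded laboratory work. The article does not say outright where swabs are taken and describes no problem with their viability. Rules on keeping a patient on one scanner are detail that an article commonly leaves to fuller documents. This objection stands in full, so the point rests on case mix, care and local dental examination.
- **The bias needs a correlation that nobody has shown.** This also stands. The 7–20% range describes earlier studies, not these sites. The illustration is crude and aligns prevalence with rate perfectly, and the listed covariates would absorb some case-mix difference. With no correlation, the simulation shows no inflation of type I error.
- **The article may condense a fuller plan.** This holds for the log-rank, Cox and mixed models, where no covariates or random-effects structure are given. A reader might infer that institute has been excluded there, but silence does not show it. It does not hold for the primary model, whose covariates are listed.
- **A random intercept is an incomplete remedy.** This is correct. It assumes that site effects are unrelated to exposure, so it removes such confounding only in part. That calls for a sensitivity analysis and is no reason to leave institute out.

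**Conclusion.** The point holds in a limited form. The primary model has a stated covariate list without institute, in a non-randomised comparison across 15 institutes. Case mix, risk-factor care and the dental examinations that supply a covariate can differ between them, and the standardised imaging and assay do not address those differences.

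The size is modest and rests on assumption. At site prevalences of 7% vs 20% and a 1.5- to 2-fold rate difference, a true IRR of 1 appears as about 1.11 to 1.19. If site prevalence and site rate are unrelated, there is little or no bias. A reader might infer that omitting institute could by itself produce the planned IRR of 4.3. The limits of 1.60 and 3.3 speak against that as long as site prevalences stay within 7–20%. What is at risk is a modest true effect, a borderline p-value, and the ability to say that the association holds within institutes.

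**What to change.** 1. Add institute as a random intercept to the primary count model and keep the overdispersion scale. SAS 9.4, which the article names, can fit this in GLIMMIX.
2. Add the same random intercept to the mixed models for MoCA, CDR and frailty, because these outcomes are rated locally.
3. Add one sensitivity analysis of the primary outcome that either conditions on institute or includes the site's Cnm-positive proportion as a covariate, because a random intercept removes between-site confounding only in part.
4. If institute is left out, say why.

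**Cost.** One variance parameter per model and one extra analysis, using data the study already holds and no new patients. Intervals become slightly wider. With about 1.8 carriers per institute, 15 fixed effects would be too sparse for the main model. Very small sites may need pooling, by a rule set before the data are analysed. In the conditional analysis, institutes with no carriers or no new microbleeds contribute nothing, so it will be less precise and should support the main result, not replace it.

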### Sample Size Estimates

The sample size was determined by feasibility, but it was ensured to be substantial enough to perform the primary analysis. According to recent studies, the general prevalence rate of Cnm-positive *S. mutans* is 7–20% (19, 25–27). Our previous retrospective study revealed that patients with Cnm-positive *S. mutans* has an incidence rate ratio (IRR) of 13.9 (4.3–44.5) when compared with patients without (20). In this study, the minimum number is 223 subjects (27 subjects with Cnm-positive *S. mutans* and 196 without) based on Cnm-positive *S. mutans* prevalence of 12%, IRR of 4.3 (equivalent to the lower limit of the 95% confidence interval), a significance level of 5%, 90% power, and a follow-up period of 2 years. Therefore, we will recruit 230 subjects with considering a dropout rate of 10%.

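### Kaplan-Meier curves for stroke and bleeding treat deaths without the event as censoring, so they modestly overstate 2-year risks; cumulative incidence is the better estimator for these secondary outcomes

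*Protocol article*

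**What the plan says.** The Statistical Analyses section of the Protocol article handles three secondary outcomes together: "the incidence of symptomatic ICH or IS, all-cause mortality, and total hemorrhagic events". For all of them it states that "the survival time curves will be derived for each group using the Kaplan-Meier method", and then that "the survival rates will be compared between the two groups using the log-rank test and Cox proportional hazard models". No other estimator of event risk is named for any of the three.

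The Outcomes section lists all-cause mortality as an outcome of its own, separate from symptomatic stroke and from major bleeding. Death from another cause is therefore not part of the stroke or bleeding endpoints.

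The Sample Size Estimates section plans for "27 subjects with Cnm-positive *S. mutans* and 196 without". That calculation concerns the primary outcome, new deep microbleeds. The article gives no expected rate or count for stroke, bleeding or death.

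**The concern.** Kaplan-Meier recognizes two states only, event or censored. When the endpoint is death from any cause, no other event can preclude it and the method is right. When the endpoint is stroke or bleeding, a patient who dies first can no longer have the event, yet the estimator counts that patient as if the event could still have been observed later. One minus Kaplan-Meier then describes a hypothetical population in which nobody dies of other causes, and it lies above the actual 2-year incidence whenever such deaths occur.

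Deaths are foreseeable here. The Eligibility Criteria admit patients within a year of a stroke or transient ischemic attack, with a modified Rankin score up to 4 and no upper age limit. What is at stake is the accuracy of the 2-year risks read off the curves. If mortality differs by Cnm status, which the study itself examines, the two curves are inflated by different amounts and the visual gap between them is distorted.

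A second, smaller matter concerns the Cox models. The exposed group is small. If it has no events at all, the ordinary estimate of the hazard ratio runs to zero and its Wald interval is unusable.

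**Working it through.** **Inputs from the article.** Group sizes 27 and 196, follow-up 2 years (Sample Size Estimates). The split reproduces: 0.12 × 223 = 26.8, so 27; 0.88 × 223 = 196.2, so 196.

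**Inputs assumed, because the article gives none.** Two-year Kaplan-Meier event risk *p* from 5% to 20%. Two-year risk *q* of death without a prior event, also 5% to 20%, on the same net scale. Constant cause-specific hazards.

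**Size of the overstatement.** With hazards λe = −ln(1−p)/2 and λd = −ln(1−q)/2, the actual 2-year incidence is

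CIF = λe/(λe+λd) × [1 − (1−p)(1−q)],

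to be compared with 1 − KM = p.

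| p (1 − KM) | q (death) | CIF | Overstatement (points) | Share of p |
|---|---|---|---|---|
| 5% | 5% | 0.500 × 9.75% = 4.88% | 0.1 | 2.5% |
| 5% | 20% | 0.187 × 24.0% = 4.49% | 0.5 | 10% |
| 10% | 5% | 0.673 × 14.5% = 9.75% | 0.25 | 2.5% |
| 10% | 20% | 0.321 × 28.0% = 8.98% | 1.0 | 10% |
| 20% | 5% | 0.813 × 24.0% = 19.51% | 0.5 | 2.4% |
| 20% | 20% | 0.500 × 36.0% = 18.00% | 2.0 | 10% |

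The range is thus about 0.1 to 2.0 points. A calculation with annual rates agrees: at 4% per year for the event, 1 − KM is 7.69%, while the actual incidence is 7.61%, 7.54%, 7.32% or 6.98% with deaths at 1, 2, 5 or 10% per year.

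**Unequal mortality.** Suppose both groups have a Kaplan-Meier risk of 10%, but deaths are 5% in one and 20% in the other. The curves coincide at 2 years, while the actual incidences differ by 9.75 − 8.98 = 0.77 points.

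**Set against sampling error.** For a 10% risk in 27 patients the standard error is √(0.1 × 0.9/27) = 5.8 points, against an overstatement of 0.25 to 1.0 points.

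**Chance of no events among 27 Cnm-positive patients.** P(0) = (1 − r)^27 for an assumed 2-year risk *r* in that group:

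- r = 2%: 58%
- r = 3%: 44%
- r = 5%: 25%
- r = 10%: 6%
- r = 20%: 0.2%

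The two problems do not peak together. Where the overstatement reaches 2.0 points (event risk 20%), an empty group is very unlikely. Where an empty group is likely (2-5%), the overstatement is about 0.05 points (2% event risk, 5% deaths) to 0.5 points (5% event risk, 20% deaths).

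**The case against.** The strongest reply is that this is one paragraph in a journal article about secondary outcomes, and that the handling of competing deaths and sparse data belongs in a full protocol or SAP that is not shown. The article never says that deaths are censored. This has force for the sparse-data fallback, which is a detail a SAP commonly settles. It has less force for the curves: the article names Kaplan-Meier for endpoints that death can preclude, and that estimator leaves no alternative to censoring. A SAP using cumulative incidence would depart from the stated method.

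It is also fair to say that the study's purpose is a relationship between Cnm-positive bacteria and small vessel disease, for which cause-specific comparisons are suitable. Guidance for prophylaxis is a hoped-for consequence in the Discussion, not the stated objective. The bias is small beside the imprecision of a group of 27. Finally, the article does not limit stroke or bleeding to non-fatal events, so a fatal hemorrhage would count as an event and only deaths without a prior event compete. All of this stands, and it keeps the point minor.

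A reader might go further and infer three things that the documents do not support:

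- **That the log-rank and Cox comparisons are invalid.** Censoring at death leaves them valid as comparisons of cause-specific hazards.
- **That only about one event is to be expected among the Cnm-positive patients.** No event rate is given. With no exposure effect, the expected count runs from 0.5 to 4.9 for assumed rates of 1% to 10% per year; one event corresponds to a rate near 1.9% per year. With 2% per year in the unexposed and a hazard ratio of 4.3 (borrowed from the microbleed calculation purely as an illustration), it is 4.3 events, with a 1% chance of none.
- **That the hazard ratio would have no usable interval.** With an empty group the Wald interval fails, but a profile-likelihood interval still has a finite upper limit and the log-rank test still works.

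**Conclusion.** The point holds for the risk curves only. Kaplan-Meier is the wrong estimator of 2-year risk for symptomatic stroke and bleeding when death is a separate outcome, and the right one for all-cause mortality. Under assumed 2-year death and event risks of 5-20% and constant hazards, the overstatement is about 0.1 to 2.0 percentage points, roughly 2-10% of the Kaplan-Meier figure, and unequal between groups if mortality differs by Cnm status. The direction does not depend on these assumptions; the size does, and the article gives no rates to narrow it.

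The primary analysis and the cause-specific tests are unaffected. Sparse events in the Cnm-positive group are a contingency that depends on an unknown rate, not a demonstrated failure. This is a minor point on secondary outcomes.

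**What to change.** Keep Kaplan-Meier for all-cause mortality. For symptomatic intracerebral hemorrhage, ischemic stroke and hemorrhagic events, report Aalen-Johansen cumulative incidence by Cnm status, with death from other causes as the competing event and a fatal hemorrhage, stroke or bleed counted as an event. Describe the log-rank and Cox results for these endpoints as cause-specific.

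Optionally, pre-specify Cox regression with Firth's penalty and profile-likelihood intervals (PROC PHREG, FIRTH option) for use if the Cnm-positive group has few or no events, so that the choice is not made after the counts are seen.

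The cost is analysis wording only. Both methods are available in SAS 9.4, the software already named, and death times are needed anyway for the mortality curve. Reported event risks become slightly lower.

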## Abstract

**Introduction:**

The role of commensal microbiota in systemic diseases, including brain diseases, has attracted increasing attention. Oral infectious diseases, such as dental caries and periodontitis, are also involved in cerebrovascular diseases and cognitive impairment. Cerebral microbleeds (CMBs) and intracerebral hemorrhage due to small vessel disease (SVD), are presumably associated with a high risk of vascular cognitive impairment and stroke. We previously reported that *Streptococcus mutans* (*S. mutans*, the main pathogen of dental caries), harboring the *cnm* gene that encodes the collagen-binding protein Cnm, is associated with the development of hypertensive intracerebral hemorrhage and aggravation of CMBs. We also proposed a mechanism by which the circulating Cnm-expressing *S. mutans* causes intracerebral hemorrhage or CMBs; it binds to denuded basement membranes mainly composed of collagen IV through damaged tight junctions or it directly invades endothelial cells, resulting in blood-brain barrier injury. In November 2018, we initiated a multicenter, prospective cohort study (RAMESSES: Risk Assessment of Cnm-positive *S. mutans* in Stroke Survivors; UMIN Clinical Trials Registry: UMIN000045559) to explore the longitudinal association between Cnm-positive *S. mutans* and CMBs with comprehensive dental findings, which should determine the effect of Cnm-positive *S. mutans* in the oral cavity on the risk of CMB development and cognitive decline.

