### Eligibility Criteria

Inclusion criteria are defined as follows: (1) patients with stroke (cerebral infarction, ICH, or subarachnoid hemorrhage) or transient ischemic attack that developed within the past 365 days; (2) patients over 40 years of age; (3) patients whose modified Rankin Scale (mRS) score is 4 or less; (4) patients who have deep ICH or at least one deep CMB on T2^*^WI performed within the past 365 days; and (5) written informed consent has been obtained from the patients themselves or the proxies. Exclusion criteria are as follows: (1) patients who are contraindicated for MRI examination because of the presence of some metallic implants, such as pacemaker devices; (2) patients with bleeding diathesis; (3) patients who participate in other intervention trials; (4) patients who cannot conduct the Montreal Cognitive Assessment (MoCA) due to severe dementia, deafness, or visual impairment; (5) patients who have no remaining teeth; or (6) patients whose participation is judged as inappropriate by the principal investigator or sub-investigators if a patient is not deemed to have capacity to provide fully informed consent or is too unwell at the time of recruitment (Table 2).

**Table 2 T2:** Eligibility criteria.

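### Cognitive and frailty change is measured from a baseline 0 to 365 days after stroke with no use of time since stroke, so remaining recovery is mixed with decline

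*Protocol article*

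**What the plan says.** - **Entry.** Eligibility Criteria admit "patients with stroke (cerebral infarction, ICH, or subarachnoid hemorrhage) or transient ischemic attack that developed within the past 365 days". No minimum interval is given. Study Design and Setting has the same window ("The study will register 230 patients who develop stroke within 1 year after onset"). Disability is allowed up to a fairly severe level: "patients whose modified Rankin Scale (mRS) score is 4 or less".
- **Time origin.** Outcomes are "assessed at baseline, 6, 12, 18, and 24 months after written informed consent is obtained", so the clock starts at consent and not at the stroke.
- **Measurement.** Psychological Examinations schedules "CDR (at baseline and 2 years), MoCA (at baseline, 1 and 2 years". The Clinical Frailty Scale is taken at baseline and 2 years only (Table 1; Clinical Frailty Scale).
- **Analysis.** Statistical Analyses compares "The changes of scores based on frailty scale scoring, the cognitive tests from baseline to 2 years" by Cnm status with generalized linear mixed models and names no covariates for them. The only covariate list belongs to the primary CMB model. It includes history of cerebrovascular disease, but neither time since the index event nor its type.
- **Aim.** The abstract says the study "should determine the effect of Cnm-positive *S. mutans* in the oral cavity on the risk of CMB development and cognitive decline".

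**The concern.** Two patients can share a baseline visit label and be at very different stages. One may be assessed soon after an ICH with marked disability, the other eleven months after a TIA. A change score taken from that visit combines two processes: recovery not yet complete at entry, and the later decline that the study wants to relate to Cnm.

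The consequences differ in kind. Within each group, average change is shifted towards improvement and its spread is increased. The comparison between groups is biased only if the amount of recovery still to come differs by Cnm status. The article gives some reason to expect this. Its Introduction cites an odds ratio of 4.5 for ICH versus ischaemic stroke with Cnm carriage, and deep ICH is by itself a route into the cohort. If ICH patients have more recovery ahead of them at entry, Cnm-positive patients would seem to decline less, which works against the cognitive effect named in the abstract.

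**Working it through.** **Figures in the plan.** The article gives no effect size, SD or power for cognition or frailty, so there is no figure to reproduce for these outcomes. Its expected group sizes do reproduce: 12% of 223 = 26.8, that is 27 positive and 196 negative (Sample Size Estimates).

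**Assumptions, none from the documents.** Entry is uniform over 0 to 365 days. Remaining recovery at entry day t is A·exp(−t/τ), with A = 1 to 2 MoCA points at onset and τ = 30 to 90 days. The SD of MoCA change is 3 points.

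**1. Recovery left in the change score.** Mean = A·(τ/365)·(1 − exp(−365/τ)).
- A = 1, τ = 30: 1 × 0.0822 × 1.000 = 0.08 points.
- A = 2, τ = 90: 2 × 0.2466 × 0.983 = 0.48 points.

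This is the shift in within-group change. For a single patient it runs from the full 1 to 2 points (entry at day 0) to at most 2 × exp(−365/90) = 0.035 points (entry at day 365).

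**2. Noise.** Entry time alone gives a between-patient SD of 0.19 (A = 1, τ = 30) to 0.51 (A = 2, τ = 90). The variance of change rises by a factor of (9 + SD²)/9 = 1.004 to 1.029. With A = 3 and τ = 90 the SD is 0.76 and the factor 1.065. This is a small loss.

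**3. Group contrast when entry time and recovery are the same in both groups.** The term in step 1 cancels, so the bias is zero.

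**4. Group contrast when stroke type differs.** Assume that 30% of Cnm-negative patients have ICH as index event and that the odds ratio of 4.5 carries over to this cohort.
- Odds in Cnm-positives: 0.30/0.70 × 4.5 = 1.929, a share of 1.929/2.929 = 65.9%.
- Difference in share: 0.659 − 0.300 = 0.359. With 20% or 40% in Cnm-negatives, the share in positives is 53% or 75% and the difference 0.33 or 0.35, so the assumed share matters little.
- Let A now be the excess recovery at onset in ICH over other index events. Bias = 0.359 × mean remaining excess = 0.359 × 0.08 = 0.03, up to 0.359 × 0.48 = 0.17 points, in favour of Cnm-positives.
- If nearly every ICH patient were assessed early, the full 1 to 2 points would apply: 0.359 × 1 = 0.36, up to 0.359 × 2 = 0.72 points.
- If the odds ratio in this cohort were 1, the shares would be equal and this source of bias would vanish.

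**5. Chance imbalance in entry time.** The SD of a uniform 365-day window is 365/√12 = 105.4 days. The SE of the group difference in mean time since stroke is 105.4 × √(1/27 + 1/196) = 105.4 × 0.205 = about 22 days.

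**6. Scale.** If 10% of 230 drop out, 207 remain, about 24.8 positive and 182.2 negative. The difference detectable with 80% power is (1.96 + 0.84) × 3 × √(1/24.8 + 1/182.2) = 1.8 points. The bias in step 4 under uniform entry is small beside this; 0.36 to 0.72 would not be negligible.

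**The case against.** **This is left to the analysis plan.** A journal article need not list covariates for secondary mixed models, and an unseen plan may include time since stroke. That stands as far as the missing covariate list goes, which is not a fault in itself. The entry window, the consent-based origin and the baseline-to-2-year contrast are fixed in the article, however, and together they put recovery into the change score. Analysts who reused the one covariate list given would not remove it.

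**Variable entry time does not by itself bias the comparison.** This is correct (working, step 3). A reader might infer that the wide window alone distorts the Cnm effect. Nothing in the article suggests that carriers enrol earlier or later than others.

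**The odds ratio may not carry over.** This also stands. Everyone in this cohort has a deep ICH or a deep CMB, and the Introduction ties Cnm to deep CMBs too, so the association with ICH could be weaker here.

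**The extremes are trimmed.** Patients unable to take the MoCA because of severe dementia, deafness or visual impairment are excluded, as are those judged too unwell. This helps in part. The second criterion is left to judgement, and neither requires recovery to be complete.

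**Adjusting for index-event type may remove part of the effect.** This is fair. The Discussion presents ICH as a consequence of Cnm-positive carriage, so ICH may lie on the causal path.

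**Conclusion.** The point holds as a weakness of the cognitive and frailty comparisons, which are secondary outcomes. The change scores mix remaining recovery with decline, and the stated analysis does nothing to separate them. The certain effects are a shift of within-group change towards improvement and a small increase in variance. Bias in the Cnm contrast is conditional on a difference by Cnm status in time since stroke or stroke type. Such a difference is plausible but not shown. With a 30% ICH share in Cnm-negatives, the odds ratio of 4.5 carried over, 1 to 2 points of excess recovery at onset, uniform entry and a 30 to 90 day recovery constant, the bias is about 0.03 to 0.17 MoCA points.

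A reader might go further and infer a bias of 0.36 to 0.72 points that masks or reverses a true effect. The documents do not support that. It requires nearly all ICH patients to be assessed early, and the article contains no recovery figures and no distribution of entry times.

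The primary outcome, the count of new deep CMBs, is not affected by this point.

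**What to change.** - In the mixed models for MoCA, CDR and Clinical Frailty Scale, include days from index stroke to baseline assessment and its interaction with visit.
- Add a sensitivity analysis of MoCA change from the 1-year to the 2-year visit. Visits run from consent, so patients on schedule are then at least 12 months past the stroke. Under the assumptions above, at most 0.035 points of recovery remain at the start of that interval.
- Report adjustment for index-event type only as a further sensitivity analysis, because ICH may lie on the causal path.
- State in the conclusions that CDR and frailty have only two time points, so recovery can be only partly separated from decline for them.

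**Cost.** Analysis-plan wording only. Eligibility already requires the timing of the stroke, and the 1-year MoCA is in Table 1. The price is a few more model terms with only about 27 exposed patients, so they should be kept few, and a shorter interval with less change to detect in the MoCA sensitivity analysis.
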